### Outcome measures

The principal outcome of interest is minutes of LPG stove use over the last 6 months of the study. This time period is of interest in order to assess the effectiveness of the intervention on sustained use rather than initial adoption. Stove use will be measured via stove use monitors (SUMs). Each stove will be equipped with SUMs, which are iButton temperature loggers programmed to collect temperature data at 10 minute intervals [64]. This leaves the memory at capacity after 2 weeks. Field staff will visit households every 2 weeks to download the data. Monitors will be used to determine minutes of stove use during that period. Biweekly visits will also serve as a quality control measure because staff can address faulty readings, typically by replacing the iButton.

A secondary outcome of interest is stove use measured via weighing of LPG cylinders with a scale. Field staff are scheduled to visit households every 2 weeks to download SUMS data. They will use this opportunity to administer an LPG stove use questionnaire and weigh cylinders with a scale during their bi-weekly visits. Weighing cylinders is a cheaper alternative to measuring stove use, but it is possible that the measurements are biased. When a cylinder is weighed, participants will be asked if they refilled the cylinder within the 2 weeks and, if so, how much. It is possible that social-desirability bias is introduced in these measurements because participants are aware of our study interests and may misreport accordingly [65]. Determining the degree of bias or measurement error by comparison to SUMS data may be useful for future studies requiring stove use measurements in Ghana or similar contexts. See Fig. 3 for a study timeline.

**Fig. 3 Fig3:**
[figure not shown]
ELAG Study Flowchart

### Data management

Field staff will administer numerous paper based surveys, and survey forms will be checked for completeness and consistency by a field supervisor. Data entry will be performed in the KHRC computer center. KHRC has well-established procedures for digitizing data and storing results in a relational database. The original paper records will be securely stored in the KHRC Data Center. Once paper records are transcribed, data will be anonymized for privacy protection. Personally identifiable information will be removed and a proprietary KHRC participant ID will link records. Clinical health information is not included in or collected by this particular study. Outside of KHRC, the only individuals permitted to access the data are those listed in the Columbia University IRB protocol. Standard KHRC and Columbia University procedures will be followed otherwise. Monthly reports providing summaries of enrollment and various field activities are discussed among the study team.

### Analysis

The primary analysis will be to examine the effect of the intervention on average stove use over the final 6 months of the observation period. Due to the nested nature of the observations, these data will be analyzed with a hierarchical linear model. The three intervention arms, consisting of the two interventions alone and one combined, will be compared to the control arm, which receives no intervention.

Several secondary analyses are also of interest. First, while the primary analysis is unadjusted for potential covariates, a secondary analysis will include covariates such as financial literacy, the number of unanticipated life events necessitating additional financial resources, ethnicity, intra-household cooperation, and household asset index. Second, additional analyses will look at the various trends across time, assessing stove use in the first 5 months of the study and over the 10 months. A third analysis will analyze sustained use across arms by demographic characteristics identified in improved cookstove adoption related systematic reviews. Finally, given that the Ghanaian government is already distributing LPG cookstoves and interested in increasing sustained use, this research is policy-relevant. Qualitative data will be collected and analyzed among key stakeholders involved in the intervention. This analysis can then be used to consider meaningful ways to scale the intervention based on existing fuel infrastructure.

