### Study eligibility & recruitment

ELAG participants are limited to participants who were enrolled in the original GRAPHS cohort and who: 1) were originally randomized to the Biolite or control arms of the study and 2) still reside in the KHRC study region (see Fig. 1). Participants are visited to assess interest in the new study, although, due to longstanding involvement with GRAPHS and other KHRC initiatives, we do not anticipate any issues reaching our recruitment goals.

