### Power

Power calculations reflect the cluster-randomized study design. Treatment is on the cluster level (2) while outcomes are on the household level (1). The outcome of the study is minutes of LPG use per day summed over a six-month period. Multilevel model power calculations with 27 clusters, 979 sample size and type I error at 5%. The mean for the reference group is estimated at 3000 min over 6 months, with equal group sizes. This is believed to be a conservative estimate based on our unpublished research in the region, which found ~ 3100 mean minutes of use over 20 weeks [42]. The effect size (Cohen’s D) is calculated with 1000 min as the pooled standard deviation, which is an overestimation based on our research. Multilevel power formulas were derived from Scherbaum, 2009 [43]. Intraclass Correlation Coefficients are unknowable given the novelty of the research, but several possibilities were modeled - visualized with the Optimal Design Plus Empirical Evidence version 3.1 software, see Fig. 2.

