### Randomization

The parent study utilized a cluster-randomized design on coarsened exact matches to assign study treatments [54]. This study re-randomized clusters employing a covariate-constrained randomization approach with several identified prognostic covariates [55, 56]. The covariate-constrained randomization approach is a powerful allocation technique to ensure balance between arms in cluster randomized trials. Baseline covariates were chosen based on prior literature and theoretical relationships (see Table 2). When covariates are continuous, balance is determined via mean differences between treatment arms. Maximum permissible imbalance is designated a priori. Given these parameters, allocation amongst arms is randomly designated if below the maximum permissible imbalance. An independent epidemiologist performed the final randomization using the *ccrand* procedure in Stata [57]. Allocation was not revealed to field staff until after baseline data collection was complete.

**Table 2 Tab2:** Covariate constrained randomization variables

Variable	Rationale
Community Asset Index	Scientific articles have shown that differential access to resources can be predictive in the uptake of new cookstove technologies (19–21).
Average Household Size	Scientific articles have shown that household size can be predictive in the uptake of new cookstove technologies (19–21).
Distance to Refueling Station	Study communities are scattered throughout the region at varying distances from the refueling center. Further distances are likely a deterrent to refuel for non-Agent delivery households, *see map*.
Households per cluster	To ensure roughly equal number of participating households per arm.

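### The primary model leaves out the four community variables used to constrain the allocation; if they predict stove use, its test is conservative and power is lost

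*Protocol article*

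**What the plan says.** On allocation, the Randomization section of the protocol article states: "This study re-randomized clusters employing a covariate-constrained randomization approach with several identified prognostic covariates". Table 2 lists four community-level variables: asset index, average household size, distance to the refueling station and number of participating households. The tightness of the constraint is not reported; the text says only "Maximum permissible imbalance is designated a priori".

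On analysis, the Analysis section says that "these data will be analyzed with a hierarchical linear model", with each of the three intervention arms compared with control, and that "while the primary analysis is unadjusted for potential covariates". Covariates enter a secondary analysis only, and the examples named are "financial literacy, the number of unanticipated life events necessitating additional financial resources, ethnicity, intra-household cooperation, and household asset index". Only the last of these is close to a Table 2 variable.

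The article mentions no randomization test within the set of acceptable allocations, and nothing else links the primary model to the constrained design.

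**The concern.** Constraining the allocation removes most of the chance imbalance on the chosen variables, so the true variance of an arm difference falls. An unadjusted model cannot see this. It estimates between-community variance from all the scatter within arms, including the part due to the balanced variables. Its standard error then describes a simple randomization that was not performed.

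At stake is precision in comparisons of 6 or 7 communities with 7. Intervals would be too wide, and a real effect could be missed in a trial that took the trouble to balance its arms.

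**Working it through.** **Inputs from the protocol article.** Table 1 cells: 7, 7, 7 and 6 communities, 979 households in all, so m = 979/27 = 36.3 households per community. Power section: type I error 5%, SD 1000 minutes. Fig. 2 caption: effects of 0.3 and 0.5 SD. The text gives no numerical power, so there is no figure to reproduce.

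**Assumptions.** ICC 0.05 or 0.10; R2 (the share of between-community variance explained by the four variables) from 0 to 0.75; allocation drawn from the best 5%, 10% or 50% of candidate allocations; two-sided test. The contrast is combined intervention (6) against control (7).

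**Step 1: SE without adjustment.** In SD units, SE = sqrt{[ICC + (1−ICC)/m] × (1/6 + 1/7)}.
- ICC 0.05: sqrt[(0.05 + 0.95/36.3) × 0.3095] = sqrt(0.0762 × 0.3095) = 0.154.
- ICC 0.10: sqrt[(0.10 + 0.90/36.3) × 0.3095] = sqrt(0.1248 × 0.3095) = 0.197.

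**Step 2: limiting case of perfect balance.** The true variance then contains only ICC × (1−R2). At ICC 0.10 and R2 = 0.50: sqrt[(0.05 + 0.0248) × 0.3095] = 0.152. The unadjusted SE would be too large by up to 0.197/0.152 = 1.29. Real constraints balance only partly, so simulation is needed.

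**Step 3: simulation of community means.** Unadjusted model on 27 − 4 = 23 df; adjusted model on 27 − 4 − 4 = 19 df; t reference.

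| Allocations kept | ICC | Effect (SD) | R2 | Type I error, unadjusted | Power, unadjusted → adjusted |
|---|---|---|---|---|---|
| best 10% | 0.10 | 0.5 | 0 | 4.7% | 68% → 63% |
| best 10% | 0.05 | 0.5 | 0 | 5.0% | 88% → 84% |
| best 10% | 0.05 | 0.5 | 0.25 | 4.1% | 88% → 90% |
| best 10% | 0.10 | 0.5 | 0.25 | 3.9% | 71% → 76% |
| best 5% | 0.05 | 0.3 | 0.30 | 3.2% | 47% → 52% |
| best 5% | 0.10 | 0.5 | 0.30 | 3.7% | 69% → 78% |
| best 10% | 0.10 | 0.5 | 0.50 | 2.8% | 69% → 85% |
| best 5% | 0.05 | 0.3 | 0.60 | 2.0% | 43% → 63% |
| best 5% | 0.10 | 0.5 | 0.60 | 2.1% | 69% → 90% |
| best 10% | 0.10 | 0.5 | 0.75 | 1.2% | 68% → 95% |

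Type I error of the adjusted test stays between 4.4% and 5.7%. At R2 = 0.10 (best 5%) the two models tie: 47% v 47% (ICC 0.05, effect 0.3) and 68% v 68% (ICC 0.10, effect 0.5). With the best 50% kept and R2 = 0.30, unadjusted type I error is 4.2% to 4.3% and the gain is about 4 to 6 points.

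**Step 4: is the constraint the cause?** At ICC 0.10 and R2 = 0.50, simple randomization gives unadjusted type I error of 5.0%, against 2.8% under the constraint. At an effect of 0.5, unadjusted power is 68% under simple and 69% under constrained allocation, so without adjustment the constraint buys almost no power. Adjusted power is 81% and 85%.

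**Step 5: in minutes.** At ICC 0.10 and R2 = 0.50 the mean model SE is 0.200 unadjusted and 0.158 adjusted. With SD 1000, the 95% half-widths are 2.07 × 200 = 414 and 2.09 × 158 = 330 minutes.

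**The case against.** The strongest defence is that the planned analysis is valid. It is prespecified, the estimate is unbiased, and on between-community degrees of freedom the type I error does not exceed 5%. That stands, and it sets the grade. A reader might infer that the primary result would be biased or falsely positive; nothing in the documents or the calculations supports this.

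Second, the gain is conditional. Adjustment spends 4 of 23 between-community degrees of freedom, and with unprognostic variables it loses power. Table 2 also does not make an equal case for all four: the reason given for households per cluster is equal arm sizes, not prognosis. Distance is justified by "Further distances are likely a deterrent to refuel for non-Agent delivery households", so its effect may differ by arm; allowing for that shrinks the gain slightly in a check (5 rather than 8 points at ICC 0.10, R2 = 0.30). This stands as a limit on size. Even so, the article itself calls the covariates prognostic.

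Third, the article fixes no reference distribution. With a normal reference, small-sample inflation offsets part of the conservatism: unadjusted type I error at R2 = 0.30 is then 4.2% to 5.5%. That masks the mismatch through a second inaccuracy and does not remove it.

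Fourth, the secondary covariates are introduced as examples, so a reader who concludes that distance, household size and cluster size are excluded from that model goes too far. They are merely not named, and a secondary model would in any case leave the primary test unchanged.

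A reader might also extend the point to the parent trial, since participants "were originally randomized to the Biolite or control arms of the study". The documents do not support this. They give neither the split of communities by parent arm nor evidence that it predicts stove use. It was not a constraining variable, so chance imbalance on it is already covered by the standard error.

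**Conclusion.** The point holds as a conditional loss of efficiency. The article states both the constrained allocation and the unadjusted primary model, so this is not a detail left to an unseen analysis plan. If the Table 2 variables predict stove use, as the protocol assumes, the unadjusted standard errors are too large and the test is conservative.

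For 30% to 60% of between-community variance explained, unadjusted type I error is roughly 2% to 4% and adjustment gains about 3 to 21 points of power. It roughly breaks even near 10% and costs about 3 to 7 points at 0%. These ranges rest on assumed ICCs, explained variance and constraint tightness, and on a t reference. The direction is secure under the protocol's own premise; the size is not. It would be too strong to say that power is certainly lost, or that adjusting is free. Severity: should be fixed.

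**What to change.** State the primary model as the hierarchical linear model with study arm plus the four Table 2 variables at community level, tested on between-community degrees of freedom (27 − 4 − 4 = 19). Alternatively, base the primary test on a permutation over the set of allocations that met the imbalance limit. Keep the unadjusted model as a sensitivity analysis, and report the imbalance limit used.

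The cost is a sentence or two in the Analysis section and about 4 between-community degrees of freedom. All four variables are already held, because they were used for the allocation. If they prove not to be prognostic, the price is the 3 to 7 points of power given above.

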## Discussion

ELAG represents a unique opportunity to understand various facets of LPG adoption and sustained use, principally the role of two distinct interventions to influence ongoing use, one via behavioral change promotion and another through fuel-access modifications. However, the large sample size, randomized design, and established cohort, allows for exploration of numerous other pivotal relationships. For example, assessing the role of gender via intra-household cooperation as a potential mediator of increasing sustained use is both innovative and instructive. Quantifying the degree to which unexpected life circumstances impedes sustained use is also novel and useful to policymakers.

Biomass cookstove use is a widespread source of air pollution, mostly in the developing world. However, much remains unknown regarding effective strategies to increase clean cookstove adoption and sustained use. Many studies to date have sought to demonstrate the health benefits of improved or clean cookstove, but have been largely unsuccessful, likely due to the difficulties of lowering exposures to health-relevant levels. Indeed, many studies have shown that exposure-reduction is a challenging endeavor [66]. Our study aims to document meaningful ways to increase adoption and sustained use, thereby reducing exposure. If successful, these strategies can then be scaled to measure the health impacts of exposure reductions.

## Abbreviations

CBSV: Community-based surveillance volunteer
ELAG: Encouraging LPG Adoption in Ghana study
GRAPHS: Ghana Randomized Air Pollution and Health Study
HAP: Household Air Pollution
KHRC: Kintampo Health Research Centre
LPG: Liquefied petroleum gas
RANAS: Risks, Attitudes, Norms, Abilities, and Self-regulation
SUMs: Stove use monitors
